## Abstract

**Background:**

Recently, we demonstrated that the Montreal Museum of Fine Arts’ (MMFA) participatory art-based activity, known as “Thursdays at the Museum,” improved the well-being, quality of life, and physical health (i.e., frailty) of older community dwellers by using a pre-post intervention, single arm, prospective and longitudinal experimental design. The present randomized clinical trial (RCT), known as the Art-Health RCT (A-Health RCT), aims to compare changes in well-being, quality of life, frailty, and physiological measures in older community dwellers who participate in “Thursdays at the Museum” (intervention group) and in their counterparts who do not participate in this art-based activity (control group).

**Methods/design:**

The current unicenter, randomized, clinical, controlled, comparative trial recruits 150 older community dwellers to two parallel arms (75 participants in the intervention group and 75 participants in the control group). The intervention is a 3-month cycle of weekly “Thursdays at the Museum,” which are structured 2-h-long art-based workshops performed in a group setting at the MMFA. The control group is composed of participants who do not take part in art-based activities, receive their usual health and/or social services, and commit to report any other activity practiced during the same time. Assessments of the primary outcome (well-being) and the secondary outcomes (quality of life, frailty, and physiological measures including heart rate, daily step count, sleep duration, and its phases) are performed on six occasions: at baseline, at the beginning of the second and third months, at the end of the third month, as well as 6 and 12 months after the last workshop. Statistical analyses are performed with the intention to treat and per protocol. Comparisons of changes in outcome measures between intervention and control groups use repeated measures tests.

**Discussion:**

Art-based activities carried out at museums have been receiving increased interest from researchers and policy-makers because of their benefits to mental and physical health. There are few robust studies, such as RCTs, that focus on older community dwellers or assess the efficacy of these participatory museum activities. The A-Health RCT study provides an opportunity to confirm the benefits of a participatory art-based museum activity on the elderly population and to show the key role played by museums in public health promotion.

**Trial registration:**

NCT03679715; Title: A-Health RCT: Effects of Participatory Art-Based Activity on Health of Older Community Dwellers; First posted date: September 20, 2018; prospectively registered.

## Background

Participation in creative art activities has been receiving increased interest in the past decade [1, 2]. It has been shown that participatory art-based activities may improve aspects of mental health such as positive emotions and self-esteem [3–6]. Art-based activities help patients, regardless of their disease, to build a sense of self, transforming the illness experience into a positive experience and improving patients’ well-being and quality of life [5–8]. Well-being, defined as a good or satisfactory condition of existence, quality of life, and health are closely related, and this relationship is important at older ages [9, 10]. Well-being is positively associated with quality of life and physical health benefits, including a decreased risk for disease, speedier disease recovery, and increased longevity [6–13]. In parallel, it has been found that art-based activities are positively associated with numerous aspects of individuals’ physical health, like a better immune system response and slower disease progression, with these effects being related to well-being improvement [3, 6–8]. These mental and physical health benefits suggest that art-based activities may be effective interventions for frailty prevention in older community-dwellers. The elderly population’s health condition is heterogeneous due to the variously combined effects of physiological aging-associated decline and morbidities [14]. Frailty, which is used to classify the health condition of older adults and their ability to respond to an intervention, is a condition of vulnerability related to an accumulation of morbidities and exposing individuals to incident adverse health events, which increase health and social costs [14–16]. The frailty process may be prevented or even reversed, especially at its onset [15]. Older individuals with mild frailty benefit the most from interventions that can promote health and prevent frailty from worsening [15]. Thus, it seems that older adults with frailty—especially those at its onset—will particularly benefit from engaging in art-based activities. There are few robust experimental studies, such as randomized clinical trials (RCT) that regard the effects of participatory art-based activities on mental and physical health and, thus, more information is needed, especially about older adults and those with frailty.

Museums have designed their spaces to create participatory art-based activity programs that can be carried out in a pleasant environment [8, 17–20]. For instance, in 2015, the Montreal Museum of Fine Arts (MMFA) developed “Thursdays at the Museum,” which is a participatory art-based activity performed by older community dwellers who live in Montreal creating art in group settings. In 2018, the effects of this participatory art-based activity on the well-being, quality of life, and frailty (i.e., physical health) of older community dwellers were examined [21]. With a pre-post intervention, single arm, prospective, and longitudinal design, we showed that the MMFA’s participatory art-based activity improved the well-being, quality of life, and frailty of older community dwellers in Montreal. Each outcome’s improvement evolved differently over the 3-month cycle of weekly art-based activities. Well-being was greater at the end of each workshop when compared to the beginning, with a similar magnitude of change throughout the cycle. In contrast, quality of life improved gradually over the course of the cycle. Finally, when comparing the cycle’s end to its beginning, the proportion of vigorous participants was greater, whereas the proportion of mildly frail participants was smaller. A major limitation of our first study was its design, as the gold standard to examine the effects of an intervention is a RCT in parallel groups.

Findings from our first study suggest that “Thursdays at the Museum” may improve older adults’ mental (i.e., well-being and quality of life) and physical (i.e., frailty) health. The relationship between well-being, quality of life, and physical health is complex. Previous studies, including our first study, suggested the existence of a chronological sequence of benefits: positive experiences induced by art-based activities improve well-being, which improves quality of life and, finally, physical health [6–13, 21]. This sequence may explain the changes in outcomes over time reported in our first study. However, the changes in well-being, quality of life, and physical health that older community dwellers experience over time and independently of any intervention are sparsely known. These aging-related changes may influence the effects specific to “Thursdays at the Museum.” We hypothesize that changes in well-being, quality of life, and frailty due to older community dwellers’ participation in “Thursdays at the Museum” (1) each have not the same profile of evolution over time; (2) are greater than those observed with aging (i.e., experienced by the older adults with or without morbidities that make up the control group); (3) are improvements of well-being, quality of life, and frailty; and (4) may persist after the discontinuation of “Thursdays at the Museum.”

## Objective

This study aims to compare changes in well-being, quality of life, physical health (i.e., frailty), and physiological measures (heart rate, daily step count, sleep duration, and its phases) in older community dwellers participating in a 3-month cycle of “Thursdays at the Museum” (intervention group) to the corresponding changes in their randomized counterparts who do not participate in this MMFA art-based activity (control group).

## Methods

### Design

The design is a unicenter (MMFA; Montreal, Quebec, Canada), clinical, randomized, controlled trial with two parallel arms (intervention and control groups) that is comparative (comparison of intervention and control groups). The participants in the intervention group participate in “Thursdays at the Museum.” The control group is composed of older community dwellers who do not participate in “Thursdays at the Museum.” They are not deprived of any indicated health or social services, and they continue to be followed by their health and social professionals. They commit to withhold participation in art-related interventions for the study period and to report any other activity practiced during the same time. Due to the nature of the intervention, participants cannot be blind to it. The principal investigator, his representatives and all staff members involved in the RCT phases (i.e., recruitment, assessment, and follow-up of participants) are blinded to the allocation of the intervention, except one staff member who is not involved in these RCT phases. Blinding is also applied after data collection (from data analysis to the reporting of results).

### Participants

#### Selection criteria

Being 65 and over, understanding and writing French or English, having Internet access at their place of living and an electronic device, having a life expectancy over 15 months, and providing and signing a written informed consent to participate in the RCT are the criteria for inclusion. The principal investigator or representatives will provide the individual with written and oral information about the study and any special considerations in the informed consent form and the consenting process in a language they can understand. The individual then signs an informed consent form. Life expectancy is estimated with a free software using socio-demographic, cardio-vascular risk factors, physical activity, and income characteristics (https://www.blueprintincome.com/tools/life-expectancy-calculator-how-long-will-i-live/). The exclusion criteria are concomitant participation in another experimental study regardless of its type; major disabilities like deafness, blindness, and gait disorders; and major neurocognitive impairment. This information is collected during the recruitment process by phone call.

#### Setting and recruitment

The Art-Health RCT (A-Health RCT) is an ongoing study carried out at the MMFA (Quebec, Canada). The participant recruitment and follow-up processes are shown in Fig. 1. Museum visitors aged 65 and over are informed by an email from the MMFA that an experimental study on the effects of “Thursdays at the Museum” is ongoing at the MMFA. Individuals who are interested in participating register on the web platform of the Centre of Excellence on Longevity (CEEXLO) using a link provided at the end of the MMFA’s email. After registration, they are contacted by phone by a representative of the principal investigator to assess the selection criteria. If they meet all criteria and agree to participate in the RCT, they are recruited. Information on non-included participants and on those who withdraw their consent and/or drop out during the 15-month period of follow-up is recorded.

**Fig. 1 Fig1:**
[figure not shown]
Flow chart of screening, recruitment, and follow-up

#### Randomization

After the baseline assessment, participants are randomly allocated to intervention and control groups using block randomization with a 1:1 ratio. The randomization list is established with the N’Query randomization software by the project manager, who is the only person able to identify participants based on their code. All investigators are blind to randomization. The project manager is not involved in the recruitment nor the follow-up of participants. He conducts the randomization process and informs the participants of to which group they are assigned. Randomization is performed the week before the first workshop.

Furthermore, a subset of participants is offered a Fitbit Alta HR (Fitbit, Inc.; San Francisco, CA, USA) to record physiological measures (i.e., heart rate, daily step count, sleep duration, and its phases). The subset is limited to 30 intervention group and 30 control group participants, determined in a second randomization that keeps the subsets as similar as possible to control for selection bias. This second randomization adopts the process used during the first randomization and the same project manager oversees it to ensure that all investigators remain blind. After the second randomization is completed, the project manager in charge of randomization provides selected participants with a Fitbit device, an assessment schedule and instructions. The project manager also installs the Fitbit application on participants’ portable electronic devices and creates their individual accounts with coded usernames.

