### Power calculation

The number of participants required for this study has been calculated to detect the expected change in WEMWBS score between the baseline assessment (M0) and the end of the 3-month cycle (M3) calculated using the formula ((score M^*n* + 1^ – score M^*n*^)/((score M^*n* + 1^ + score M^*n*^)/2)) × 100. The expected difference between intervention and control group was estimated 5.2 ± 10.3 based on a previous study [21]. A free sample size calculator (http://www.sample-size.net/sample-size-means/) was used*.* The minimum number of participants to show an absolute difference between the 2 groups (i.e., intervention and control groups) with alpha = 5% and power = 90% is of 63 per group. Thus, the theoretical total number of participants for the study is 126. Anticipating an 18% rate of participant loss during the follow-up period, the total number of participants required is 150 (75 participants per group).

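### The Fitbit subset is picked by arm after allocation and the device is then offered in an open trial, so selective refusal is not guarded against; settling willingness at baseline would close the gap cheaply

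*Protocol article*

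**What the plan says.** All of the procedure is in the protocol article, Methods, Randomization. After baseline, "participants are randomly allocated to intervention and control groups using block randomization with a 1:1 ratio". The project manager holds the list: "He conducts the randomization process and informs the participants of to which group they are assigned". The timing is tight: "Randomization is performed the week before the first workshop".

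The next paragraph adds the device step: "a subset of participants is offered a Fitbit Alta HR". Its size is capped by arm: "The subset is limited to 30 intervention group and 30 control group participants". The members are "determined in a second randomization that keeps the subsets as similar as possible to control for selection bias". On method: "This second randomization adopts the process used during the first randomization". The same project manager hands out the devices once this second step is done.

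The Design section says that participants cannot be blinded. The Outcomes section lists the physiological changes as the sixth secondary outcome, restricted to subset members who have recordings. The article does not say whether participants already know their arm when the device is offered, or which variables the subsets should be similar on.

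**The concern.** A subset defined as so many from each arm can only be drawn once the arms exist. The device is offered, so it can be refused. If the person already knows the arm, the decision to accept comes after randomisation and may depend on it. Controls who have just learned that they will not attend the workshops may refuse more often than intervention participants, and for other reasons. If the more active or more motivated controls are the ones who accept, the two sets of wearers differ in traits that drive step count and sleep. Restricting the analysis to people with recordings carries that difference into the result.

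The similarity clause does not help. The first randomisation is described as plain blocks with no balancing variable, so reusing that process adds no control over participant characteristics. The clause names no variables, and it acts on who is drawn, whereas the exposure lies in who accepts.

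**Working it through.** **Order of steps.** Baseline assessment, then 1:1 allocation, then a draw of up to 30 within each arm, then the device. Allocation before the draw follows from the definition of the subset. Disclosure before the offer is the natural order of the text but is not stated; equally, nothing rules it out.

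**Count.** The trial size is given as "the total number of participants required is 150 (75 participants per group"), so the subset is 30/75 = 40% of each arm. Between arms, 30:30 is 1:1, which agrees with the stated ratio.

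**Does drawing after allocation cause bias by itself?** I simulated 10,000 trials of 75 v 75 with no true effect and a background trait correlated 0.5 with the outcome, comparing 30 per arm by t test.

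| Selection of the 30 per arm | Mean difference (SD) | Two-sided 5% error |
|---|---|---|
| Random draw within each arm | -0.004 | 5.0% |
| Acceptance depends on the trait, same way in both arms | -0.003 | 4.6% |
| Acceptance depends on the trait in controls only | -0.12 | 7.1% |

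In the last two rows refusers are replaced until 30 accept. In the third row, acceptance is 80% in the intervention arm, unrelated to the trait, and about 67% in controls, with a log-odds slope of 0.8 per SD of the trait. Simulation error near 5% is about sqrt(0.05 × 0.95 / 10,000) = 0.2 percentage points, so the first two rows are compatible with 5%.

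**How large could it be?** The article gives no acceptance rates, so these are assumptions: everyone in the intervention arm accepts; control acceptance is 90%, 75% or 60%; the log-odds of acceptance rise by 0.5 or 1.0 per SD of the trait. The shift d is the mean of the trait among accepting controls. Then error = P(|Z + d / sqrt(2/30)| > 1.96), with sqrt(2/30) = 0.258.

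| Control acceptance | Shift if the outcome is the trait itself | Error | Shift at correlation 0.5 | Error |
|---|---|---|---|---|
| 90% | 0.05 to 0.09 SD | 5.4% to 6.4% | 0.02 to 0.05 SD | 5.1% to 5.4% |
| 75% | 0.12 to 0.21 SD | 7.5% to 13% | 0.06 to 0.11 SD | 5.6% to 7.0% |
| 60% | 0.19 to 0.33 SD | 11% to 25% | 0.09 to 0.17 SD | 6.6% to 9.9% |

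Example: 0.12 / 0.258 = 0.465, and P(Z > 1.495) + P(Z < -2.425) = 0.067 + 0.008 = 7.5%.

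All these figures are for a comparison of levels. The planned outcome is percentage change from M0, which removes stable differences in level but not a different trend over time. The documents give nothing from which the remainder could be computed.

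**The case against.** The case against is substantial, and several parts stand.

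- A reader might infer that a 1:1 process cannot yield 30 out of 75, because 1:1 within an arm gives 75/2 = 37.5. The text does not support this. In the Randomization section, 1:1 is the ratio of intervention to control, which 30:30 meets. The subset is also capped at 30 per arm, so even a within-arm 1:1 list could be stopped there.
- A reader might infer that the physiological comparison loses the protection of randomisation outright. It does not. A random sample from each randomised arm remains comparable, even after disclosure, as the first simulation row shows. Bias needs refusal that is both arm-dependent and prognostic, and the article does not report any.
- A reader might take it as stated that the offer follows disclosure, or read the similarity clause as hand-picking. The first is an inference from the order of the text. The second goes beyond the text, which calls the step a randomisation; the clause may only describe the purpose of randomising.
- Acceptance rates and slopes are assumed, and the larger error rates describe levels rather than the planned change.
- Rules for refusals are operational detail that the full protocol may hold; their absence from an article is not a fault.

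What does not fall is the stated sequence: selection by arm, an offer that can be refused, participants who cannot be blinded, and analysis of those with recordings. The article says that this step controls selection bias. As described, it addresses who is drawn but not who accepts.

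**Conclusion.** The concern holds in a limited form. The subset is selected after allocation and offered in an open trial, with nothing that keeps acceptance independent of the arm, so the stated control of selection bias is not secured. Under the assumptions above, the effect runs from negligible (90% control acceptance) to a shift of about 0.17 SD and an error near 10% (60% acceptance, steep slope, correlation 0.5). It would be larger only if the selecting trait were almost the outcome itself, and change from M0 would reduce it. If acceptance is near complete or follows the same pattern in both arms, there is no bias to speak of.

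The reach is one secondary outcome family in at most 60 participants. The primary outcome, change in WEMWBS, is untouched. The reason to act is that a better procedure costs almost nothing.

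**What to change.** 1. At the baseline visit, which already takes place before allocation, ask each participant whether they would wear the device.
2. Draw the 60 at random from the willing.
3. Use device (yes/no) as a stratum of the 1:1 block randomisation. With 60 and 90 in the strata, this gives about 30 + 30 and 45 + 45, hence 75 per arm, apart from any incomplete last block.
4. Disclose the arm only after these steps.
5. Replace the similarity clause with this random procedure.
6. Analyse all 60 as randomised, do not replace later refusals, and report them by arm.

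The cost is one extra baseline question and a re-ordering of steps by the same project manager with the same software. The small downside is that the subset represents people willing to wear a device; since the device is offered, that is already so.

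If enrolment is complete, report the order actually used and the offers and refusals by arm, and label the physiological comparison as one among acceptors, open to selection after allocation.

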### Intervention

“Thursdays at the Museum” is the participatory art-based activity examined in this RCT. This hands-on activity consists of workshops during which 30 individuals create art as a group. Study participants assigned to partake in workshops are separated into two equal groups, with one group meeting on Tuesdays and the other on Wednesdays. These participants meet weekly in a room at the MMFA dedicated to the 2-h workshop. The total duration of a “Thursdays at the Museum” cycle is 3 months. Each month, a different topic is explored through 4 consecutive workshops. The topics are abstract painting, live model drawing, and stained-glass painting. Each workshop is supervised by two cultural mediators. They manage the interactive hands-on art activities, with special attention given to creativity, handcrafting techniques, and fine motor skills. Each workshop is standardized, consisting of three consecutive phases: presentation of the art activity’s objective, choice of medium, and communication of technical advice to participants.

### Assessment

#### Baseline assessment

The baseline assessment is performed with all participants (intervention and control) during a first meeting in a dedicated room at the MMFA. It is a standardized interview performed by a representative of the principal investigator and is carried out before (M0) the first workshop, at the time when participants sign the written consent form. All measurement types and their times of use are shown in Table 1. All questionnaires and scales used are reliable and previously validated. No feedback on assessment results is shared with participants.

**Table 1 Tab1:** Assessed domains, instruments and time points

Domains	Instruments	Time points								
		Baseline (M0)		Follow-up						
		Before first workshop	After first workshop	M1		M2		M3		M9 and M15
				Before fifth workshop	After fifth workshop	Before ninth workshop	After ninth workshop	Before twelfth workshop	After twelfth workshop	
Ability to use a computer	CPQ	X								
Socio-demographic characteristics		X								X
Frail condition	CESAM	X		X		X			X	X
Well-being	WEMWBS	X	X	X	X	X	X	X	X	X
Quality of life	EQ-5D	X		X		X			X	X
Physiological measures		X		X		X			X	X
Physician consultation Emergency room visit and hospitalization		X		X		X			X	X

*M* month, *M0* baseline assessment, *M1* first month, *M2* second month, *M3* thrid month, *M9* 6 months after the end of the intervention, *M15* 12 months after the end of the intervention, *CPQ* computer proficiency questionnaire, *CESAM* Centre of Excellence Self-AdMinistered questionnaire, *WEMWBS* Warwick-Edinburgh Mental Well-being Scale, *EQ-5D* EuroQol-5D

First, the computer proficiency questionnaire (CPQ), which assesses respondents’ ability to use a computer, is performed in paper format [22]. Its scores range from 5 (i.e., never tried) to 30 (i.e., can do very easily). Second, socio-demographic characteristics including age, sex, and place of living are recorded using the CEEXLO web platform. Third, frailty is assessed with the digital short form of a self-administered questionnaire: The Centre of Excellence Self-AdMinistered questionnaire (CESAM, Table 2) [23]. This questionnaire is filled out by participants under the supervision of the principal investigator’s representatives. The 20 items that make up the CESAM explore several domains, including weight loss and its magnitude; polypharmacy, defined as a number of therapeutic classes taken on a daily basis ≥ 5; vision, hearing, and memory problems; use of home support (i.e., family, friend, and/or professional); the 6-item activities of daily living (ADL) scale and the 4-item instrumental activities of daily living (IADL) scale [24]; mood, assessed using the question, “How do you feel today?” with three possible answers (happy, unhappy, and neither one nor the other); practice of regular physical activity (e.g., walking and bicycle), defined as at least 1 h per week in the past month; and history of falls in the past 12 months. Each CESAM item is close-ended (i.e., yes, no, or choose a specific answer). Automatically, two scores are calculated: (1) a frailty score, ranging from 0 (i.e., best health and functional condition) to 18 (i.e., worst health and functional condition) and (2) a categorization of frailty into one of four stages (vigorous with a score between 0 and 3, mild frailty with a score between 4 and 7, moderate frailty with a score between 8 and 12, and severe frailty with a score above 12). Fourth, EuroQol-5D (EQ-5D) is used to assess participants’ quality of life [25]. This assessment is comprised of two parts. The first is a questionnaire containing five questions coded from 1 (i.e., no issue) to 5 (i.e., worst issue), resulting in total scores ranging from 0 (i.e., no issue) to 25 (i.e., worst issue). The second part of EQ-5D is a visual analog scale (VAS) that explores how good or bad participants perceive their health to be. This scale ranges from 0 (i.e., worst health a participant can imagine) to 100 (i.e., best health a participant can imagine). Fifth, the Warwick-Edinburgh Mental Well-Being Scale (WEMWBS) is used to assess mental well-being [26]. This questionnaire consists of 14 positively worded items with five response categories that cover several aspects of positive mental health. Its scores range from 14 (i.e., none of the time) to 70 (i.e., all the time).

**Table 2 Tab2:** Self-administered question items and additional questions for follow-up

Item	Answer	
Have you unwillingly lost weight in the past year?	Yes	No
If yes, was the loss of weight above 3 kg/6 lbs?	Yes	No
How many different types of drugs do you take on a daily basis?	- 0	
	- 1–4	
	- 5–9	
	- ≥ 10	
Do you have vision problems?	Yes	No
Do you have hearing problems?	Yes	No
Has someone close to you expressed concern about your memory?	Yes	No
Do you receive home care support?	- Family	
	- Friend	
	- Professional	
If yes, from whom?	Yes	No
Do you need help with your grooming (brushing teeth, hair, shaving, applying make-up)?	Yes	No
Do you need help with bathing or taking a shower?	Yes	No
Do you need assistance when getting dressed?	Yes	No
Do you use mobility aides for walking or transferring (cane, walker, wheelchair)?	Yes	No
Do you need help with your meals: Shopping for food, meal preparation, assistance in eating	Yes	No
Do you need help when using the telephone?	Yes	No
Do you need assistance when taking public transportation?	Yes	No
Do you need help for managing medications on your own?	Yes	No
Do you need help to pay your bills and manage your finances?	Yes	No
Are you incontinent (urine and/or stool)?	Yes	No
How do you feel today?	- Happy	
	- Unhappy	
	- Neither one nor the other	
Do you feel energetic?	Yes	No
Do you do regular physical activity (walking, swimming, cycling, etc.) at least 1 h per week in the past month?	Yes	No
Have you fallen in the past year (at least one fall)?	Yes	No
Additional questions asked to the participants before completing the CESAM at M1, M2, and M3	Yes	No
Since you last filled out this questionnaire, have you visited your doctor?	Yes	No
If yes, was this visit unplanned?	Yes	No
Since you last filled out this questionnaire, have you been hospitalized?	Yes	No
If yes, was this hospitalization unplanned?	Yes	No
Did you visit the emergency room?	Yes	No

Physiological measures including heart rate, number of daily steps, and sleep duration and its phases are recorded with a Fitbit Alta HR. This device is built like a watch and continually records data for periods of 5 consecutive days (2 days before the workshop, the day of the workshop, and 2 days after the workshop). No biological samples are collected in this RCT.

